### Tele.TAnDem intervention

Members of both TEL and F2F will receive twelve 50-minute sessions of an individual cognitive-behavioral therapy (CBT) provided by trained psychotherapists within 6 months. The first four sessions will take place at weekly intervals and six further sessions will follow at fortnightly intervals. The two last sessions will be conducted at monthly intervals. Both TEL and F2F sessions will be offered by the same therapists to minimize person effects.

The theoretical concept of the intervention is based on the principles and methods used in CBT. The therapy strategies have been especially adapted for caregivers of people with dementia. The standardized and manual-based intervention [5] consists of 10 different therapy modules which can be used and combined by the therapist according to the individual needs of each participant: 
*Basic elements.* Basic elements cover creating therapeutic alliance, structuring of each session and handling of crises.*Problem analysis.* An individual problem analysis to identify the participants’ main problem areas in the caregiving situation and individual therapy goals is conducted.*Psychoeducation.* The therapist provides information on dementia and its course to help participants handle the caregiving situation as well as supporting them in accepting the consequences of dementia.*Strengthening problem solving abilities.* Through problem-solving training, participants are instructed and supported in their individual problem-solving process.*Changing dysfunctional cognitions.* Through Socratic dialog and guided discovery, the therapist and participant work out alternative ways of thinking as well as possibilities to test and transfer these alternative thoughts to real life.*Increasing the use of social and/or professional support in home-based care.* Possibilities of professional and informal help are discussed. The process of allowing and accepting help is discussed using the CBT strategy of cognitive restructuring.*Coping with change, grief, and loss experience.* Central topics are coping with personality changes caused by dementia, the loss of the personal relationship and the resulting feelings of grief. In this context, emotion-based coping-strategies, acceptance of the illness and its resulting changes, as well as experiences of loss are of high importance.*Creating enjoyable positive activities.* Potential incentives are to be increased through the following mechanism: description of the link between positive activities and mood by means of a weekly diary, lists of health-promoting activities, planning of activities, and promoting their implementation.*Improving social skills.* Elements of the social skills training, such as behavioral observation, role-play, and behavioral experiments are performed.*Evaluation.* Changes and goals achieved are summarized and plans for the future discussed.

### Primary outcome measures

*Depressiveness.* A self-developed thermometer scale (0 to 100, vertical) and the Allgemeine Depressionsskala (ADS) [6] will be used to assess depressiveness. The 20 items of the ADS cover emotional, motivational, cognitive, and somatic aspects. Implementation and evaluation are standardized, Cronbach’s *α* is.89.

*Burden of care.* A self-developed thermometer scale (0 to 100, vertical) will be used to assess burden of care.

*Health complaints.* Physical health complaints will be assessed on four domains (fatigue, stomach problems, heart problems and joint pain) by using the Gießener Beschwerdebogen [7]. Besides the values of the four subscales, all 24 items can be used to calculate the subjectively experienced pressure of complaints. Regarding quality criteria, the Gießener Beschwerdebogen has standardized implementation and evaluation procedures, good internal consistency (Cronbach’s *α*.82 to.88 for the subscales and Cronbach’s *α*=.94 for the total scale) and is normed.

*Ability to solve problems relating to focused problem areas.* Problem-solving ability will be measured by Goal Attainment Scaling [8], a non-standardized manual-based instrument providing process-orientated information on how far participants are from reaching individual therapy goals. Caregivers and therapists will rate the goal attainment in the last therapy session.

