**Methods/Design:**

If participants live in the area of one of the study centers (Jena, Berlin, Munich) and indicate that attendance of a face-to-face therapy is possible, they will be assigned to the face-to-face group. The other participants will be randomized to receive either telephone-based cognitive-behavioral therapy or usual care. Data will be collected at baseline, post-intervention, and at a 6-month follow-up. The primary outcomes will be depressiveness, burden of care, health complaints, and problem-solving ability. The secondary outcomes will be anxiety, quality of life, violence in caregiving, utilization of professional assistance, and cost effectiveness.

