In the present study, Tele.TAnDem will be implemented in established care provision structures (Alzheimer Society) for the first time. The aim of our study is to assess the effectiveness of this integrated intervention in a randomized controlled trial. The primary objective is to evaluate whether telephone-based cognitive-behavioral therapy (TEL) improves depressiveness, burden of care, health complaints, and problem-solving ability compared to usual care. The secondary objectives are to evaluate whether (1) TEL is as effective as face-to-face cognitive-behavioral therapy (F2F), (2) a two-day training program (8h) in Tele.TAnDem for behavioral therapists is sufficient to achieve an adequate and effective implementation of the intervention, (3) the TEL intervention is a cost-effective or possibly even cost-saving alternative compared to usual care, and (4) TEL increases the use of professional support by family caregivers of people with dementia compared to the control group.

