## Methods/Design

### Design

This study is a non-blinded two-armed parallel randomized controlled trial with a third non-randomized group. Participants will be asked whether they reside in the area of a study center and can participate in the F2F. If this is the case, they will be assigned to the F2F group. If this is not the case, they will be randomly assigned to the TEL group or usual care. Random allocation will be on a 1:1 ratio basis but separated for gender and will take place after the baseline assessment. All participants will receive information materials on care and dementia. Assessments will be conducted at baseline (T0), post intervention (T1) and a 6-month follow-up (T2) (Figure 1). The TEL group will receive 12 psychotherapy sessions on the phone, whereas the F2F group will receive 12 psychotherapy sessions in direct contact in one of the participating treatment centers.

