## Discussion

This study will evaluate whether TEL improves depressiveness, burden of care, health complaints, and problem-solving ability compared to usual care and assess whether TEL is as effective as F2F. One strength of this study is its robust design and follow-up assessment allowing evaluation of the long-term effects of TEL. For the first time, it will be possible to test intervention effects of TEL in established care services.

However, there will also be several challenges in this study. In particular, enrolling a sufficiently large sample in the F2F group will be a major difficulty, which we hope to overcome by recruiting via different media and by directly assigning participants to F2F.

The F2F sample will be especially selective, as it will consist of an exclusively urban and mobile population. Since possible F2F participants will be selected from the overall recruited sample, the remaining subsample being randomized will potentially be more rural and less mobile than the original sample recruited.

To ensure adequate and homogeneous application of therapeutic strategies, extensive training prior to implementation, application through CBT-qualified therapists, regular supervision (4 to 6 times per year) and documentation of the implementation will be essential strategies. To determine treatment integrity, independent CBT-qualified therapists will assess psychotherapeutic competence and adherence in randomly selected audio and video recordings of the sessions.

In case the intervention is terminated prematurely, an attempt will be made to continuously include the participant in the data collection. To avoid selective dropout in the control group, this group will receive an incentive. Blinding is not possible in the design of the proposed study, since both the family caregivers and the therapists will know whether a therapy is conducted. To nevertheless guarantee an independent assessment of intervention efficacy, the data collection will be performed by researchers who are not involved in the therapy.

In summary, this will be the first study to test the implementation of telephone-based cognitive-behavioral therapy in established care provision structures in a randomized controlled trial. If TEL proves to be effective in improving primary outcomes, our results will be relevant to practice. Hence, TEL could be used on a large scale. Thus, the results of the study will be used to improve support services for family-caregivers.

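### Problem-solving ability is a primary outcome against usual care, but its only described measure is a rating of therapy goals in the last therapy session, so no usual-care value is described

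*Protocol article*

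**What the plan says.** The abstract (Methods/Design) states: "The primary outcomes will be depressiveness, burden of care, health complaints, and problem-solving ability". The Background section gives the primary objective as whether TEL "improves depressiveness, burden of care, health complaints, and problem-solving ability compared to usual care", and the opening of the Discussion repeats this comparison.

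Under Primary outcome measures, problem-solving ability has one instrument, Goal Attainment Scaling, described as giving "process-orientated information on how far participants are from reaching individual therapy goals". The occasion and raters are fixed in the next sentence: "Caregivers and therapists will rate the goal attainment in the last therapy session".

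The section on the Tele.TAnDem intervention shows where the goals come from. In the problem-analysis module of the therapy, "An individual problem analysis to identify the participants’ main problem areas in the caregiving situation and individual therapy goals is conducted". The same section gives the twelve sessions to TEL and F2F. For all groups alike, the Design section says: "All participants will receive information materials on care and dementia". It also schedules assessments at T0, T1 and T2.

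The Discussion answers the lack of blinding by saying that "the data collection will be performed by researchers who are not involved in the therapy".

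**The concern.** A comparison between randomised arms needs the outcome in both arms. Here the outcome is defined by three things that belong to the therapy: goals agreed in it, a therapist to rate them, and a final session in which to do so. The article describes none of the three for usual care, and it names no other measure of problem-solving ability.

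If the plan is followed as written, there is either no test of this primary outcome or an end-of-therapy score from treated participants alone. Such a score could be read as an effect against usual care, which it is not.

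**Working it through.** **1. Setting the sections side by side**

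| Element of the measure | TEL | F2F | Usual care |
|---|---|---|---|
| Individual therapy goals (problem-analysis module) | yes | yes | none described |
| Therapist as rater | yes | yes | none described |
| Last therapy session | yes | yes | none described |
| Randomised comparison | yes | no | yes |

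The two groups that can supply ratings are TEL and F2F. F2F is not randomised, and TEL versus F2F is a secondary objective. The pair named in the primary objective, TEL and usual care, has ratings on one side only: 0 of the 118 planned usual-care participants have a described value. By count of constructs, this is 1 of 4 primary outcomes.

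**2. Can the planned analysis fill the gap?**

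The Data analysis section handles missing data by full information maximum likelihood. That method uses observed values to inform unobserved ones. When an outcome is never observed in one arm, nothing in the data identifies that arm's mean, so the arm difference cannot be estimated. An analysis of variance or a χ² test between the arms has the same need for control data.

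**3. The sample size**

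Inputs from the Sample size section: two groups, three measurement points (m = 3), α = .05, power .80, ρ = .50, and 82 per group (N = 164). The effect is called small without a number. I assume f = 0.10, the value at which the stated size reproduces.

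- For the group-by-time interaction, λ = f²·N·m/(1 − ρ) = 0.01 × 164 × 3/0.5 = 9.84.
- The degrees of freedom are (2 − 1)(3 − 1) = 2 and (164 − 2)(3 − 1) = 324.
- Power at α = .05 is 0.805, and N = 164 is the smallest even total that reaches .80. The stated 82 per group reproduces.
- For dropout, 82/0.70 = 117.1, rounded up to 118. This also reproduces.

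The calculation therefore supposes three measurements in each of two groups. Goal Attainment Scaling as described supplies one in TEL and none in usual care, so no group-by-time test can be formed on it.

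**4. Illustration of the multiplicity cost**

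The article promises a correction across the primary outcomes but names no method. Assuming Bonferroni, with λ and degrees of freedom as above:

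- Three tests, α = .05/3: power 0.665.
- Four tests, α = .05/4: power 0.627.
- Difference: 0.665 − 0.627 = 0.038, about 4 percentage points for each testable outcome.

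**The case against.** The strongest defence is that this is a condensed article and that the T0, T1 and T2 schedule covers every outcome. The article does not say that the last session is the only occasion, so a reader who infers that usual care can never have a value goes further than the text. What can be said is that no value is described. Beyond that wording, the defence fails. The article itself fixes instrument, raters and occasion for this outcome, and they differ from the general schedule. A rating by controls at T1 would still need goals set beforehand, and goals are set only in therapy. A later analysis plan cannot create data that were not collected.

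Several stronger readings are tempting and should not be drawn:

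- **That the power loss measures the harm.** Bonferroni, f = 0.10 and a family of three or four are all assumptions. Depressiveness has two instruments and the complaints questionnaire has subscales and a total, so the size of the family is not given. An outcome that yields no p-value need not use up any α.
- **That the outcome fits none of the planned models.** Latent change models are planned only for longitudinal continuous data. A single rating could go into an analysis of variance if control values existed.
- **That ratings would exist only for therapy completers.** Someone who stops early may still have had a last session, and the Discussion plans to try to keep such participants in the data collection.
- **That the therapist rating is a second contradiction.** The statement on independent data collection may refer to T0, T1 and T2, and caregivers rate too. It is a tension: therapists would rate the result of their own treatment.

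**Conclusion.** The point stands as a contradiction within the article. Problem-solving ability is to be compared with usual care, but the described measure exists only where there is therapy. The randomised comparison cannot be made on one of the four primary constructs, with 0 of 118 planned control values described. This rests on the article's text alone and on no assumed figure. The mismatch between one rating and three measurement points adds to it.

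A reader might infer that the whole primary objective falls, or that exactly a quarter of it does. The documents do not support the first, since the other three primary outcomes keep their randomised comparison. The second counts four constructs as equal, which the article does not state. The figure of about 4 percentage points of power is illustrative and does not carry the conclusion.

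**What to change.** Remove Goal Attainment Scaling from the primary TEL versus usual-care outcomes. Delete problem-solving ability from that objective in the abstract, Background and Discussion, and from the set of outcomes corrected for multiple testing. Report it as a process outcome in TEL and F2F, with caregiver and therapist ratings shown separately because the therapist is not independent of the treatment.

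The cost is one fewer primary outcome and a documented amendment to the protocol and the registration. No new data collection is needed.

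If problem-solving ability must stay primary, name a measure collected in both randomised arms at the planned assessments. One possibility is to elicit individual goals from everyone at T0, before allocation, and have caregivers rate them in the later telephone interviews. This has drawbacks that should be stated. It may give usual care part of the problem-analysis module, and the goals may differ from those set in therapy. It must also be settled before enrolment, because baseline goals that were not elicited cannot be recovered.

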### Secondary outcome measures

*Anxiety.* Anxiety symptoms will be measured by using the anxiety subscale of the Hospital Anxiety and Depression Scale [9]. This instrument is standardized and normed and has good internal consistency (Cronbach’s *α* is.80 for the anxiety subscale).

*Quality of life.* The WHOQOL-Bref [10] is a standardized and normed questionnaire with 26 items measuring subjective physical and mental well-being as well as satisfaction with social relations and the environment. Cronbach’s *α* is between.77 and.87, implementation and evaluation are standardized. The items of the WHOQOL-BREF will be changed in tense from present to past because the focus is on respondents’ recall of the last two weeks.

*Violence and aggressiveness in caregiving.* Verbal and latent violence and aggressiveness in caregiving will be assessed by a standardized questionnaire assessing the frequency of such behaviors [11]. Cronbach’s *α* for this 7-item instrument is.80.

*Utilization of professional assistance.* An instrument, developed and piloted in a sample of caregiving relatives, will be used to assess utilization of professional assistance in three areas (demand, utilization, and barriers to utilization).

*Cost effectiveness.* The cost-effectiveness analysis will be conducted from the perspective of statutory health insurance with a time horizon of 6 months. This will consist of the costs of the intervention and of the health care utilization of the caregiving relatives. The latter will be assessed by the FIMA questionnaire [12]. In addition, time spent on informal care will be measured by a modified version of the Resource Utilization in Dementia (RUD) questionnaire [13,14]. As a measure of effectiveness, subjectively rated health status of caregiving relatives and quality of life, measured through the EQ-5D [15], will be used.

*Background.* Based on the experience of our previous studies [4,16], a questionnaire will be used, assessing not only the socio-demographic characteristics of carers and people with dementia, but including further aspects. For family caregivers, detailed conditions of the care situation, diseases, sleep quality, physical activity, and medication will be assessed. For the person with dementia, type of dementia, other diseases, and care services used will be assessed.

*Adequateness of 8h training.* The therapists’ rating of adequateness of the 8-hour training program and the supervision will be assessed through a semi-structured interview with each therapist after the end of all therapy sessions.

### Sample size

Based on results of meta-analyses [1,17,18], we can expect interventions for caregiving relatives of people with dementia to have small to medium effects on the mental and physical health of caregivers (*d*=0.14 to 0.41). Results from the previous project [4] similarly indicate that this telephone-based intervention has small to medium effects (*f*=0.18 to 0.29).

Hypothesizing a small effect size in a two-group design with three measurement points, an *α* of.05, a power (1−*β*) of.80, and a *ρ* of.50, we need a sample of *n*=82 per group [19]. Therefore, we aim to have 164 participants in the randomized groups. Assuming a dropout rate of 30%, we plan to recruit 118 persons in each randomized group. Additionally, we aim to recruit as many people for the F2F group as possible (with *n*=118 as cut-off criterion).

### Data analysis

The data will be analyzed with SPSS version 22.0 (IBM Corp., Armonk, NY) and MPlus version 7.0 (Muthén & Muthén, Los Angeles, CA). Data cleaning and analyses will be performed using SPSS/Mplus syntax operations. Possible baseline differences between trial arms will be statistically tested and further analyses will be adjusted for imbalances in the baseline scores. The primary analysis will be by intention to treat. For the primary outcomes, analyses will be corrected for multiple testing.

As sensitivity analyses, completers of all assessments will be analyzed separately. Hypotheses tests will be performed at *α*=.05. The numeric outcomes will be analyzed using analyses of variance; categorical outcomes will be analyzed using *χ*^2^-tests. Additionally, latent change model analyses will be performed for continuous longitudinal outcome data. To handle missing data, full information maximum likelihood estimation will be conducted in MPlus. As part of the questionnaire adaptation, factor, reliability, and correlation analyses will be performed.

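### For TEL versus usual care, baseline adjustment should be fixed in advance and not made to depend on significance tests of baseline differences

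*Protocol article*

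**What the plan says.** The rule stands in the protocol article, Data analysis: "Possible baseline differences between trial arms will be statistically tested and further analyses will be adjusted for imbalances in the baseline scores". The sentence speaks of trial arms in general. It gives no cutoff for what counts as an imbalance, and it does not separate the randomised comparison from the one with F2F.

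The same section names the models: "The numeric outcomes will be analyzed using analyses of variance", and then "Additionally, latent change model analyses will be performed for continuous longitudinal outcome data". No covariates are listed for either.

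Under Design, the TEL and usual-care groups are formed by chance: "Random allocation will be on a 1:1 ratio basis but separated for gender and will take place after the baseline assessment". F2F participants are assigned without randomisation.

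The Sample size section starts from this premise: "Hypothesizing a small effect size in a two-group design with three measurement points". With α = .05, power .80 and ρ = .50 it arrives at 82 per group, 164 in total, and 118 per group after 30% dropout.

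**The concern.** Between randomised arms, a test of baseline difference asks whether chance produced a difference that is already known to come from chance. The answer says nothing about whether the baseline score should be in the model. What justifies adjustment is that the baseline score predicts follow-up, and the plan itself assumes that it does (ρ = .50).

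Two things are at stake. First, the primary model is chosen from the data, and the adjustment set can differ from one primary outcome to the next. Second, where no imbalance is declared, the trial forgoes precision that its T0 data could supply. That matters in a trial planned for a small effect at 80% power.

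**Working it through.** **Inputs.** From Sample size: 82 per group, α = .05, power .80, ρ = .50, and d = 0.14 to 0.41 from meta-analyses. Assumptions made here: two-sided tests, SD 1 at every assessment, the same ρ between all pairs of assessments, f = 0.10 for a small effect, and p < .05 as the cutoff for an imbalance. No correction for multiple outcomes is applied.

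**1. The plan's own figure.** Repeated-measures group-by-time test, m = 3, N = 164:
- λ = f²·N·m/(1 − ρ) = 0.01 × 164 × 3/0.5 = 9.84
- df = 2 and (164 − 2) × 2 = 324
- power = 80.5%, and N = 164 is the smallest even total that reaches 80%
- dropout: 82/0.70 = 117.1, rounded up to 118

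The figures reproduce. A between-groups test over three assessments also gives N = 164 if f = 0.18. On either route T0 is one of the three measurements.

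**2. One follow-up time, fixed adjustment.** Variance of the analysed score:
- post score: 1
- change score: 2(1 − ρ) = 1
- baseline-adjusted (ANCOVA): 1 − ρ² = 0.75

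Power = Φ(d/(σ√(2/82)) − 1.96), with √(2/82) = 0.1562. For d = 0.41: 0.41/0.1562 = 2.625, so Φ(0.665) = 74.7%. With adjustment, 2.625/√0.75 = 3.031, so Φ(1.071) = 85.8%.

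| d | post or change score | ANCOVA | gain (points) |
|---|---|---|---|
| 0.14 | 14.4% | 17.8% | 3 |
| 0.20 | 24.8% | 31.5% | 7 |
| 0.30 | 48.4% | 60.2% | 12 |
| 0.41 | 74.7% | 85.8% | 11 |

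**3. The test-triggered rule, simulated** (20,000 trials per setting, 82 per group, ρ = .50, adjust only if the baseline test has p < .05):

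| d | rule, post-score base | always ANCOVA | rule, change-score base | always ANCOVA |
|---|---|---|---|---|
| 0 (type I error) | 4.6% | 5.2% | 4.2% | 4.8% |
| 0.20 | 24.7% | 31.1% | 24.1% | 30.6% |
| 0.41 | 75.8% | 85.3% | 75.3% | 84.6% |

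The test fires in about 5% of trials, so power stays close to that of the unadjusted analysis. False positives do not increase.

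**4. Against the group-by-time test of step 1.** Let v be the pattern of the effect at T1 and T2. The covariance matrix of the two change scores is S = [[1, 0.5], [0.5, 1]]. After regression on T0 it is A = [[0.75, 0.25], [0.25, 0.75]]. Adjustment multiplies λ by v′A⁻¹v / v′S⁻¹v, with the df left as in step 1.

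| effect at T1, T2 | ratio | λ | power | gain over 80.5% (points) |
|---|---|---|---|---|
| one follow-up only (1, 0) | 1.5/1.333 = 1.125 | 11.07 | 85.2% | 5 |
| halved at one follow-up (1, 0.5) | 1.375/1 = 1.375 | 13.53 | 91.7% | 11 |
| equal at both (1, 1) | 2/1.333 = 1.5 | 14.76 | 93.8% | 13 |

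**5. Dependence on ρ.** Starting from 80% power at one follow-up:

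| ρ | gain over post score (points) | gain over change score (points) |
|---|---|---|
| .3 | 3.6 | 13.5 |
| .5 | 9.9 | 9.9 |
| .7 | 17.5 | 6.0 |

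**6. Gender.** With assumed correlations of 0.1 to 0.3 with the outcome, gender alone moves 80.0% to between 80.4% and 83.6%. On top of the baseline score it moves 89.9% to between 90.2% and 92.4%.

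**The case against.** The strongest reply is that the plan already uses the baseline. The sample size rests on three assessments including T0, and the latent change models use T0 as well. This stands in part. A reader might infer that the baseline score would be used in only about 5% of trials, or that the loss is a flat 10 points. The documents support neither. The 5% depends on a cutoff that they do not state, and a single figure near 10 holds only for ρ = .50 and a one-time comparator with about 80% power. Even so, the group-by-time test gains 5 to 13 points from adjustment. A latent change model that regresses change on T0 would recover most of the loss, but the article lists these models as an addition and does not say that they are built that way.

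A second reply is that the sentence may also serve the F2F comparison. That is fair: F2F is not randomised, so differences there need not be chance and looking for them has a purpose. The sentence nevertheless makes no distinction, and so it also covers TEL versus usual care.

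Three further inferences are tempting and should not be drawn:
- **Gender is left out of the model.** The article lists no covariates, so gender is neither included nor excluded, and a condensed article may leave the list to the full plan. Its share of the power is small.
- **The rule produces false positives.** Simulated type I error is 4.2% to 4.6%.
- **Every outcome can be adjusted for its T0 value.** Under Primary outcome measures, Goal Attainment Scaling is scored at the close of therapy and no T0 rating is described.

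Finally, the sentence could be read as descriptive tests followed by adjustment in every case. That is not its natural sense. If it is what was meant, the fix is only a clarification.

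**Conclusion.** The point holds for the randomised comparison of TEL with usual care. It concerns a rule that the article states, not a detail left to a fuller plan. The harm is a primary model chosen after seeing the data, together with lost precision. Validity of the test is not in question.

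The size is best given as a range. At 82 per group and ρ = .50, the gain is about 3 to 12 points over d = 0.14 to 0.41 against a one-time post-score or change-score analysis, and roughly 5 to 13 points against the three-assessment test. These figures rest on equal correlations between assessments, f = 0.10 as a small effect, and α = .05 without the planned correction for multiple outcomes. The simulated rule also rests on p < .05 as the trigger. The plan should be changed, because the remedy is nearly free.

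**What to change.** In Data analysis, for TEL versus usual care:
- Delete the significance tests of baseline differences as a basis for adjustment.
- State that each outcome with a T0 score is analysed with that score as a covariate, whatever the observed balance. This covers the ADS, the two thermometer scales, the Gießener Beschwerdebogen and the secondary scales measured at T0.
- State that gender, the allocation stratum, is also a covariate.
- State that Goal Attainment Scaling is exempt, since no T0 score is described for it.
- If a power gain is quoted, give it as a range with its ρ and effect pattern.

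Comparison of baseline characteristics may stay for the non-randomised F2F comparison, in a sentence of its own.

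The cost is a few sentences of text, with no new data and no additional participants.

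### The 80% power is calculated at an uncorrected alpha of .05, but the four primary outcomes will be corrected for multiple testing; per-outcome power is about 63% under Bonferroni

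*Protocol article*

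**What the plan says.** The Sample size section of the protocol article sets out one calculation: "Hypothesizing a small effect size in a two-group design with three measurement points", an alpha of .05, "a power (1−*β*) of.80" and a correlation of .50 between repeated measures. The result is "we need a sample of *n*=82 per group", so 164 in the two randomized groups, raised to 118 per group for 30% dropout. The section mentions neither the number of primary outcomes nor any adjustment of alpha.

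The Abstract, Background and Primary outcome measures sections name four primary outcomes: depressiveness, burden of care, health complaints and problem-solving ability. Depressiveness has two instruments: "A self-developed thermometer scale (0 to 100, vertical) and the Allgemeine Depressionsskala (ADS) [6] will be used to assess depressiveness".

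The Data analysis section states: "For the primary outcomes, analyses will be corrected for multiple testing". It names neither the method nor the number of tests, and it gives .05 as the level for hypothesis tests. It also specifies an intention-to-treat primary analysis, with full information maximum likelihood for missing data.

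**The concern.** The two sections use different error rates for the same tests. A correction across several primary outcomes makes the criterion for an individual outcome stricter than .05, at least at some steps. Power worked out at .05 for a single test is then too favourable for each corrected test.

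Type I error is not at stake, because the correction is promised. What is at stake is how a null result is read. If one of the four outcomes shows no significant difference from usual care, readers will set that result against a stated 80% chance of detecting a small effect. The committed analysis may offer a good deal less.

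**Working it through.** **Inputs.** From the Sample size section: two groups, m = 3 measurements, correlation ρ = .50, alpha .05, power .80, 82 per group (N = 164), 30% dropout, 118 recruited per group. From the Data analysis section: a correction over the primary outcomes, of which there are four. Assumption: the article gives no number for the small effect, so I take f = 0.10.

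**1. Reproduce the plan's figure.** For the group-by-time interaction in a repeated-measures analysis of variance:

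- λ = f² × N × m / (1 − ρ) = 0.01 × 164 × 3 / 0.5 = 9.84
- degrees of freedom: 2 and 2 × (164 − 2) = 324
- power at alpha .05 from the noncentral F distribution: 80.5%

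With N = 162 the power is 79.98%, just short of 80%, so N = 164 is the smallest balanced total that reaches it. The dropout step also reproduces: 82 / (1 − 0.30) = 117.1, rounded up to 118.

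**2. Does this depend on f = 0.10?** A between-group test with f = 0.18, the lower end of the range quoted from the earlier project, also returns 82 per group:

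- λ = f² × N × m / (1 + (m − 1)ρ) = 0.0324 × 164 × 3 / 2 = 7.97
- degrees of freedom: 1 and 162
- power at .05: 80.1%

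The documents do not say which test was meant, so I carry both.

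**3. Apply a correction at 82 per group.**

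| Tests corrected for (Bonferroni) | Alpha per test | Interaction, f = 0.10 | Between-group, f = 0.18 |
|---|---|---|---|
| 1 (as in the plan) | .05 | 80.5% | 80.1% |
| 3 | .0167 | 66.5% | 65.7% |
| 4 | .0125 | 62.7% | 61.7% |
| 5 | .01 | 59.7% | 58.6% |

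Five tests would arise if both depressiveness instruments were counted. Three would arise if one outcome had no randomized comparison. Goal attainment might be such a case, since it is rated in the last therapy session.

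A check that needs no effect size: a two-sided test with exactly 80% power at .05 has power Φ(1.960 + 0.842 − 2.498) = Φ(0.304) = 61.9% at .0125.

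**4. Less strict procedures.** I simulated four outcomes, each with 80% power at .05 and a real effect (normal approximation, correlation between outcomes 0 to 0.9). Average power per outcome is 69–73% under Holm, 73–75% under Hochberg and 75–78% under Benjamini–Hochberg.

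**5. If nobody were lost.** With complete data on 118 per group (N = 236), the interaction test at .0125 has 82.6% power and the between-group test 80.7%.

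**The case against.** **The method is left open.** A condensed article may leave the correction procedure, the number of tests and the measure chosen per outcome to the full protocol or analysis plan. That stands, and their absence is not the point here. The article does state the alpha, the power, the sample size and the commitment to correct, and those four do not fit together.

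**63% is not a bound.** A reader might infer that power falls to 63% or lower. That goes too far. For four tests Bonferroni is the least favourable of the procedures tried, and the others average 69–78% if all four effects are real. Power falls below about 62% only if more than four tests are counted. Power to find at least one significant outcome of four under Bonferroni is 74–98%, depending on the correlation, so it can exceed 80%. The sample-size section does not claim that target, though.

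**The sample may carry more information than 82 per group.** Since 118 are recruited and dropouts' partial data are used, the realised power should lie somewhere between the values at 82 and at 118. This also stands, but the plan presents 82 as the number it needs.

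**The effect may be larger.** The earlier project is cited as showing that "this telephone-based intervention has small to medium effects", with f from 0.18 to 0.29. If f = 0.18 applied to the interaction test, 82 per group would give 99.7% power even at .0125. The plan nevertheless sizes the trial for a small effect, and its 80% refers to that.

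**Inflated familywise error.** A reader might also infer that as many as ten tests are planned, by counting every instrument, subscale and rater, and that familywise error would exceed 5% if only four were corrected for. The documents do not support this. The wording on the complaints questionnaire, "Besides the values of the four subscales, all 24 items can be used to calculate the subjectively experienced pressure of complaints", describes what the instrument offers and does not commit to five primary tests. Nothing says that the correction would count fewer tests than are performed.

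**Conclusion.** The point holds as an inconsistency between the Sample size and Data analysis sections. The figures 82, 164 and 118 are calculated correctly from the stated inputs, but they rest on an alpha that the committed analysis does not use for each outcome. At 82 per group the power per outcome is about 63% under Bonferroni over four outcomes (66.5% over three, about 60% over five measures). Under Holm it averages about 69–73% if all four effects are real. Every correction tried, when applied at 82 per group, gives less than the stated 80%.

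These sizes rest on reading small as f = 0.10, or on f = 0.18 with a between-group test. The two readings agree to within about one percentage point. The Holm figures also assume equal, real effects on all four outcomes. Partial data from dropouts could narrow the gap by an amount that the documents do not allow one to calculate.

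**What to change.** Reconcile the two sections. In the sample-size section, name the correction that will be used and restate the power per outcome for it, with the numerical effect size and the test it refers to. This changes only wording and needs no added recruitment. Its cost is a less favourable stated power.

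Alternatively, prespecify a fixed sequence. The first primary outcome is then tested at the full .05 and keeps about 80% power with 82 per group. The cost is that each later outcome can be tested confirmatorily only if those before it succeed.

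Keeping 80% per outcome under Bonferroni over four would instead take 112 analysed per group with the interaction test (112 / 0.70 = 160 recruited) or 117 with the between-group test (117 / 0.70 = 167.1, so 168 recruited). I give these figures for scale and do not recommend the increase.
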